### **Expected Outcomes of the Study**

This is a pilot investigation study. We primarily hope to inform estimates of the potential impact of mobile-phone based nudging systems for vaccines. If successful, similar programs would ideally be tested more rigorously through a larger study, or directly be incorporated into government programs.

### **Sample Size Calculation**

According to the latest Demographic and Health Survey from Ghana, about 50% of children in the Northern region receive both Bacillus Calmette–Guérin (BCG) and Polio vaccines within the first 30 days after delivery. We hypothesize that this proportion can be increased to 80% with either intervention

(reminder-only and incentives). Assuming 20 children in each cluster, and an intra-class correlation coefficient ( $\rho$ ) of 0.05, a sample size of 100 children is required in each active treatment arm (reminder-only and incentives) and in the control communities for comparison, to achieve power 0.9 at alpha 0.05. With a crude birth rate of 40, we expect 20 births in each community within six months of baseline for the average village with a population of 1000, which means that the targeted sample size for the active treatment program (100 per active treatment arm) should be achieved in less than six months.

The endline survey will be conducted in all communities in the three arms and will attempt to enroll all women who delivered a newborn in the previous 12 months. This will additionally allow us to compare outcomes of interest across treatment groups and in the pre- initiation and study intervention periods. We anticipate this will include approximately twice the number of births expected in the 6-month intervention period (600). To account for woman who may have been missed during the intervention period, refused to participate, or moved into the community after initiation, we propose a maximum of 750 woman for the endline survey.

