## Study Design Overview

The study will be designed as an open label cluster-randomized controlled study with three arms: a control arm, a reminder-only arm, and a reward arm. During the intervention phase community volunteers will be appointed to register all births in 10 randomly selected treatment communities. In each active treatment arm, an estimated 100 women across five villages will be enrolled in a proactive program. In intervention group A, participating women will receive reminders about vaccinations recommended at birth via mobile phones. In intervention group B, participating women will receive encouragement from a community-appointed volunteer to complete vaccinations recommended as well as a small cash reward for completing the recommended vaccinations. An estimated total of 200 women in the 10 treatment villages will receive one of the two study-initiated program interventions. No volunteer will be appointed to register births in the 5 control-arm villages and no woman in the 5 control-arm villages will be actively enrolled nor receive a pro-active program intervention during the intervention phase.

After the intervention phase is complete, an endline population-based household survey will be conducted in the 15 study villages to evaluate the effect of the intervention programs. The survey will enroll all consenting woman who have delivered a live-born baby in the last 12 months and reside in one of the 15 communities in the three study arms (10 intervention communities and 5 control communities). Based on a crude birth rate of 40 and an average village size of 100-1500 people, we estimate enrolling approximately 600-750 women in the endline survey. The endline survey will be used to compare the coverage of recommended early newborn vaccinations, and the proportion of births accurately and completely registered in each arm.

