## Methodology

To assess the feasibility and effectiveness of the proposed early vaccination support platforms, we will conduct a pilot study in 15 rural communities in Northern Ghana. The 15 communities will be divided into 3 groups: 1) a **reminder-only intervention group** (Intervention Group A, 5 communities), 2) an **incentivized reward group** (Intervention Group B, 5 communities); and a **control group** (5 communities). Approximately 200 mothers (100 per treatment arm) will be enrolled in intervention programs across the two treatment groups.

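### The stated power of 0.9 ignores the small number of villages: with five per arm, the protocol's own inputs give about 0.80 to 0.87

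*Protocol*

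**What the plan says.** The protocol's Sample Size Calculation starts from Demographic and Health Survey data that "about 50% of children in the Northern region receive both" vaccines in the first 30 days, and continues: "We hypothesize that this proportion can be increased to 80% with either intervention". The clustering inputs are stated openly: "Assuming 20 children in each cluster, and an intra-class correlation coefficient" "of 0.05, a sample size of 100 children is required in each active treatment arm" "and in the control communities for comparison, to achieve power 0.9 at alpha 0.05". The section makes no allowance for the number of villages or for villages of different size.

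Other sections fix the rest of the design. Methodology divides 15 communities into three groups of five and adds: "Approximately 200 mothers (100 per treatment arm) will be enrolled in intervention programs across the two treatment groups". Sample Selection and Randomization assigns arms at village level. Data Management and Statistical Analysis plans logistic regression by GEE with robust variance and cites two papers whose titles concern small-sample robust variance and GEE with few clusters.

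Village size appears in two forms. Study Design Overview assumes "an average village size of 100-1500 people", while the selection criterion in Sample Selection and Randomization is 1000 to 20000 people.

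**The concern.** The required 100 per arm is what results from inflating an individually randomised sample size by a design effect and keeping the normal critical value of 1.96. That is a fair approximation with many clusters. Here each comparison with control rests on ten villages, and the between-village variance must be estimated from them. An analysis that holds its type I error at 5% therefore needs a larger critical value (2.31 on 8 df, 2.18 on 12 df), which costs power.

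At stake is how the result is read. The protocol implies a 10% chance of missing a true 30-point gain. If the real chance is nearer 13% to 20%, an inconclusive comparison carries less evidence against the intervention than the protocol suggests.

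**Working it through.** **Inputs.** From Sample Size Calculation: control 0.50, intervention 0.80, 20 children per village, ICC 0.05, 100 per arm, alpha 0.05, power 0.9. From Methodology: five villages per arm. The protocol does not state sidedness. Two-sided is assumed, because that is what reproduces the figure.

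**1. Reproduce the protocol's figure.**
- Design effect = 1 + (20 − 1) × 0.05 = 1.95. Effective n per arm = 100 / 1.95 = 51.3.
- Individual-level n, pooled variance under the null = (1.96 × √(2 × 0.65 × 0.35) + 1.2816 × √0.41)² / 0.30² = 51.0. Times 1.95 = 99.5 per arm, which matches 100.
- Power at effective n 51.3: z = (0.30 × √51.3 − 1.96 × √0.455) / √0.41 = 1.29, so power = 0.90.
- With unpooled variance throughout, the normal approximation gives 0.919.

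**2. Same inputs with a t reference.** Degrees of freedom are 10 − 2 = 8 for two arms of five villages, or 15 − 3 = 12 for a common variance over three arms.
- Unpooled: SE = √(0.41 × 1.95 / 100) = 0.0894; noncentrality = 0.30 / 0.0894 = 3.355.
- Pooled: SE = √(0.455 × 1.95 / 100) = 0.0942; noncentrality = 0.30 / 0.0942 = 3.185.

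| Reference | Critical value | Power, unpooled | Power, pooled |
|---|---|---|---|
| t, 8 df | 2.31 | 0.835 | 0.80 |
| t, 12 df | 2.18 | 0.868 | 0.83 |

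With unpooled variance, the intervention proportion detectable at 90% power against 50% is about 83% (8 df) or 81% (12 df), not 80%.

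**3. Check against the planned type of analysis.** Beta-binomial simulation, equal villages of 20, ICC 0.05, 40,000 replicates per scenario:

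| Test | Power | Type I error |
|---|---|---|
| GEE, uncorrected robust variance, z | 0.916 | 0.116 |
| GEE, variance × k/(k − 1), t on 8 df | 0.792 | 0.049 |
| GEE, variance × k/(k − 1), t on 12 df | 0.827 | 0.060 |
| t-test on village means, 8 df | 0.824 | 0.053 |

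Here k is the number of villages per arm. Power near 0.9 appears only with the test whose type I error is more than twice the nominal 5%.

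**4. Unequal villages (sensitivity only).** The protocol gives no coefficient of variation (CV), so the values here are assumptions. Design effect = 1 + ((1 + CV²) × m − 1) × 0.05, with mean births m = 20 and unpooled variance:
- CV 0.3: design effect 2.04, power 0.82 (8 df) to 0.85 (12 df).
- CV 0.5: design effect 2.20, power 0.79 to 0.83.

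The answer depends on mean size as well as CV. At a crude birth rate of 40, assuming sizes uniform over each stated range:
- 100 to 1500: mean 800 people, 800 × 0.040 × 0.5 = 16 births in six months, CV 0.51, power 0.75 to 0.79.
- 1000 to 20000: mean 10,500 people, 210 births, CV 0.52, power 0.94 to 0.96.

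**5. ICC sensitivity.** At ICC 0.10 (assumed, equal villages of 20) the design effect is 2.90 and power is 0.67 to 0.71.

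**The case against.** The strongest reply is that nothing has been miscalculated. The protocol declares its inputs, applies a standard design-effect formula and gets the answer that formula gives. That stands: a reader might infer an arithmetic slip, and there is none. The fault is a normal reference applied to ten villages per comparison.

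Second, the analysis section cites small-sample GEE papers, so the authors know the issue, and the exact correction can be left to an analysis plan. That also stands as regards method. It does not rescue the power figure, because a correction that restores the 5% error rate lowers power, and the sample size section contains no allowance for it.

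Third, balancing villages at randomisation and the births before initiation that the endline survey collects may recover some precision. They may, but the sample size section neither claims nor quantifies a gain.

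Fourth, Expected Outcomes of the Study describes a pilot meant mainly to inform estimates, and no rule is tied to a null result. This limits the consequence. One cannot say that a null result would be misread, only that the stated power would invite it.

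A reader might also infer that realistic variation in village size brings power down to 0.79 to 0.83. The documents do not support that as a finding. It joins an assumed CV of 0.5 to a mean of 20 births, whereas the two stated population ranges, taken as uniform, give 0.75 to 0.79 and 0.94 to 0.96.

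**Conclusion.** The point holds for the design as the protocol specifies it: five villages of 20 births per arm, ICC 0.05, 50% against 80%, two-sided 5%. Power is about 0.80 to 0.87, not 0.9, and the chance of missing the hypothesised effect is about 13% to 20%, not 10%. The spread reflects the choice of 8 or 12 degrees of freedom and of pooled or unpooled variance; corrected GEE in simulation falls at the lower end, 0.79 to 0.83. No variation in village size is assumed in these figures.

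The effect of unequal villages cannot be settled from the protocol, because its two population ranges conflict and neither comes with a distribution. The ICC of 0.10 is likewise an outside assumption and serves only to show sensitivity. The shortfall is moderate and the study is a pilot, so this calls for a corrected statement, not a redesign.

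**What to change.** Keep the sample and replace the power statement in Sample Size Calculation with wording such as:

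> *With 5 villages of 20 births per arm and an ICC of 0.05, power to detect 80% against 50% at two-sided alpha 0.05 is about 0.80–0.87 once the small number of villages is allowed for.*

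Name the reference distribution and degrees of freedom behind the figure, and match them to the small-sample correction intended for the GEE analysis.

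Reconcile the village-size range in Study Design Overview (100 to 1500) with the selection criterion in Sample Selection and Randomization (1000 to 20000). Then add unequal village size as a labelled sensitivity analysis, for example mean 20 births with CV 0.3 (0.82 to 0.85) and CV 0.5 (0.79 to 0.83). A value at ICC 0.10 (0.67 to 0.71, equal villages) is optional.

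The cost is one rewritten paragraph, one reconciled range and a less favourable power figure. No extra enrolment is needed.

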All mobile communications will include a note stating that if the woman prefers to stop receiving additional reminders or information she can flash (briefly call) the study phone line and they will call her back at no cost to her, so that she can request to stop receiving messages. She will also be informed that she can send a simple “STOP” text message to the same mobile number which sent the reminder (or voice message). Messages will continue to be sent to the woman through approximately the first two weeks of newborn life. The duration of follow-up with enrolled woman will be two weeks after enrollment in the study. Community birth registration volunteers will not contact enrolled participants in this arm (or women who meet eligibility criteria but chose not to be enrolled) after the completion of the birth registration and informed consent procedure is completed.

Enrolled participants in this arm will not receive any monetary compensation, incentive or reward for participation.

**Intervention arm B (“incentives”)** relies more directly on community volunteers. In the incentives arm, community volunteers will similarly register all births in their community during the intervention phase. The volunteers will receive a 2 cedis phone credit reward for each birth registered in their community.

**All women who reside in the community and have given birth to a live-born newborn in the previous week are eligible for enrollment.** Volunteers will contact mothers as soon as possible after birth and will introduce the study purpose and procedures and ask if the woman may be interested in participating. If the woman is interested the volunteer will guide them through the informed consent process and will describe in more detail the study purpose and procedures and answer any questions the woman may have about participation. If the woman then agrees to participate and signs the written informed consent document they will be enrolled in the study (see *Informed Consent Incentives*). No incentive will be provided to the volunteer or to the mother on the grounds of study enrollment.

Mothers will be informed that the program aims at improving early vaccination coverage for newborns, and that they will receive a small reward (2 cedis) if their baby receives both the BCG and the first dose of polio vaccination within the first two weeks of newborn life.

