### ***Endline Survey***

To assess the reach of the program platforms as well as the relative effectiveness of the reminder and incentive-based activities, we will conduct an endline survey at the end of the six-month active study implementation phase, in each of the two intervention areas (10 communities each) and in the control area (5 communities) which did not receive any study-related interventions.

Surveyors will visit all households in the 15 communities and will identify households in which a woman who has given birth in the previous 12 months resides. If no household member is available at the time the surveyor visits, or a household member is available and reports that a birth occurred in the previous 12 months but that the mother is not currently available, the surveyor will return to the household up to two additional times to attempt to make contact. If any member of the household requests that the surveyor not return, this will be noted and no future visits will be conducted. If a potential participant or screened and enrolled participant requests that the surveyor return at another more convenient time, the surveyor will return up to two additional times to attempt to complete the screening and enrolment or the interview process.

**All women who reside in the community and have given birth in the previous 12 months will be eligible to participate in the endline survey.** Among eligible women, surveyors will describe the purpose and procedures of the survey and ask if the woman is available and interested in participating. If the woman is interested, the surveyor will guide her through the informed consent process. If the woman

is unavailable at this time, surveyors will return to the household up to two additional times to attempt to make contact and/or complete the survey. If the woman provides informed consent (see *Informed Consent Endline Survey*), the surveyor will engage in a brief interview with the woman using a structured survey tool, with data captured on an electronic tablet.

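### Infants whose mothers moved into a study village after the one-week enrolment window are not separated out, so by default they enter that village's arm and its volunteer-reporting denominator

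*Protocol*

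**What the plan says.** **Who is surveyed.** The Endline Survey section sets eligibility by residence when the surveyor calls: "All women who reside in the community and have given birth in the previous 12 months will be eligible". The Study Design Overview does the same, and adds that the survey will be used to compare early vaccination coverage and birth registration by arm. Under Sample Selection and Randomization, arm is a property of the village.

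**Who can be reached.** The intervention text, under Community Volunteer Appointment and Birth Registration, limits enrolment to a short window. For arm B: "All women who reside in the community and have given birth to a live-born newborn in the previous week are eligible for enrollment". The arm A wording is almost the same.

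**Who is expected.** The Sample Size Calculation anticipates about 600 births over 12 months and sets a maximum of 750 women. It gives three reasons for the margin: women missed during the intervention period, and women who "refused to participate, or moved into the community after initiation".

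**What is measured.** Primary and secondary outcomes defines the primary outcome as BCG plus at least one polio dose within 28 days of delivery. The secondary outcome is the percentage of births found by the endline survey that volunteers had reported.

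No section mentions where the mother lived at the birth or in the weeks after it. The only split described is by calendar time (before initiation against the intervention period, in the Sample Size Calculation), and that does not identify movers.

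**The concern.** A woman who delivers elsewhere and moves into an intervention village when her infant is more than a week old can no longer be enrolled. If the infant is already past 28 days, the primary outcome was settled before she arrived. She is nevertheless eligible for the survey, and with arm attached to village and no rule to the contrary, her infant is compared as a member of that arm.

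Two quantities are at stake. The vaccination contrast is pulled toward no effect, by an amount that depends on migration and not on how the programme works. The volunteer-reporting rate also falls short of its true value, because these births enter its denominator but the local volunteer had no opportunity to report them. The protocol says this rate is of particular interest to the national registry.

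Residents who were missed or who refused are a different matter. Their village's programme could have reached them, so they belong in the comparison.

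**Working it through.** **Inputs, all from the Sample Size Calculation.**
- Control rate 0.50: "about 50% of children in the Northern region receive both" vaccines in the first 30 days.
- Intervention rate 0.80: "We hypothesize that this proportion can be increased to 80% with either intervention".
- Cluster size 20: "Assuming 20 children in each cluster".
- Intra-class correlation and size per arm: "of 0.05, a sample size of 100 children is required in each active treatment arm".
- Error rates: "to achieve power 0.9 at alpha 0.05". Sidedness is not stated; two-sided reproduces the plan.
- Endline ceiling 750 against 600 expected births.

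**Step 1: reproduce the plan's figure.** Two proportions, pooled variance under the null, no continuity correction:

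n = [1.960 × √(2 × 0.65 × 0.35) + 1.282 × √(0.25 + 0.16)]² / 0.30² = 51.01

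Design effect = 1 + (20 − 1) × 0.05 = 1.95. Then 51.01 × 1.95 = 99.5, which is the stated 100. Rounding up to 52 first gives 101.4, or 102. Power at 100 per arm (effective size 100/1.95 = 51.3) is 0.902. The planning figure stands.

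**Step 2: dilution.** Let m be the share of surveyed births in an intervention arm that belong to late movers. Assume these infants have the 50% control rate. The expected rate in the arm is then 0.50 + 0.30 × (1 − m), so the effect is 30 × (1 − m) points.

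**Step 3: excluding late movers instead.** The effect stays at 30 points. The arm falls to 100 × (1 − m) births and the cluster to 20 × (1 − m), so the design effect is 1 + [20 × (1 − m) − 1] × 0.05. At m = 5% the effective size is 95/1.90 = 50.0.

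**Step 4: reporting rate.** If every birth that could be reported is reported, the measured rate is 1 − m.

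| m (assumed) | Effect, movers kept | Power at 100 per arm | n per arm for 90% power | Power, movers excluded | Perfect reporting scores |
|---|---|---|---|---|---|
| 0 | 30.0 | 0.902 | 102 | 0.902 | 100% |
| 5% | 28.5 | 0.865 | 114 | 0.894 | 95% |
| 10% | 27.0 | 0.820 | 127 | 0.886 | 90% |
| 15% | 25.5 | 0.769 | 145 | 0.876 | 85% |
| 20% | 24.0 | 0.713 | 164 | 0.865 | 80% |

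The last row is (750 − 600)/750 = 150/750 = 20%. It would need the entire margin to be late movers, spread evenly over arms and over the 12 months of births. At every assumed m above zero, excluding late movers costs less power than keeping them. The power figures use the plan's own normal approximation and serve to compare the rows.

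**The case against.** The strongest reply is that survey eligibility is not an analysis rule. The protocol never says that movers count as treated. Data Management and Statistical Analysis names the model but defines no analysis set, and interviewing broadly and then restricting the analysis is sound practice that a statistical analysis plan, not shown here, may well adopt. A reader might infer that the protocol assigns movers to the treated group; it does not say so. What stands is the default. The secondary denominator is written in the protocol as the births the survey identifies. A later plan could remove late movers only if residence around the birth is recorded, and the descriptions of survey content under Endline Survey and Ethical Considerations do not mention it. The attached questionnaire is not reproduced and may already ask.

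Three other stronger readings also fail.
- **Everyone who moved in after initiation is misclassified.** Not so. A woman who arrived while pregnant, or within a week of delivery, meets the enrolment rule in either arm.
- **The 150 extra places estimate migration.** They are attributed jointly to missed, refusing and moved-in women, with no split.
- **The gap between birth and interview is up to 12 months for births that could have been treated.** Six months of intervention, a 30-day wait and about two months of survey put it at about nine months at most. Older births fall before initiation.

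It is also fair that this is a pilot meant to inform estimates, that dilution would not by itself create a false positive, and that volunteers are asked to report births in their own communities, so a denominator of local births may be what was intended. These points limit the weight of the concern but do not supply the missing definition.

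**Conclusion.** The point holds in a limited form. The protocol has no rule for infants whose mothers moved in after the one-week enrolment window. By default those infants enter the new village's arm and its reporting denominator.

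The size depends on a share the documents do not give. At an assumed 5%, the effect falls from 30 to 28.5 points, power from 0.902 to 0.865, and perfect reporting shows as 95%. The 20% figures (24 points, power 0.713, 80%) mark an upper bound and should not be read as an expectation. All of this assumes that late movers have the control rate. The likely direction is toward no effect, but a late move from an intervention village to a control village, or between the two intervention arms, would also put an infant in the wrong group.

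The true share may be small. The case for acting is that the remedy is cheap, and that Study Duration and Follow-Up rules out further contact after the survey, so an item not asked then cannot be recovered.

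**What to change.** 1. Check that the endline questionnaire records the village of residence at the birth and, for women who moved in, the date of the move. Add the item if it is absent.
2. In Endline Survey, Primary and secondary outcomes, and Sample Size Calculation, base the arm comparison and the volunteer-reporting denominator on intervention-period births to women resident in that study village at delivery or within the first week after it. This matches the protocol's own enrolment window; a cut at delivery alone would drop women whom the programme may enrol.
3. Apply the residence rule in the same way in all three arms, regardless of enrolment or refusal, so that missed and refusing residents stay in.
4. Keep interviewing later movers, and report them separately or in a sensitivity analysis.

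The cost is at most one item, with a date for movers, in a 10–15 minute interview, and a short definition in three sections. The downside is slightly fewer analysed births: at an assumed 5%, power is 0.894 against the planned 0.902.
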